### 4.2 Risks and inconveniences for the study subjects

#### 4.2.1 Study drug (all participants)

##### 4.2.1.1 Acute effects

Since the study drug will be administered intravenously, a peripheral intravenous catheter will be placed. This may cause discomfort related to skin puncture by the needle. When the venous catheter is removed a small hematoma may develop that, however, will disappear by itself within a few days.

In previous studies, naloxone given in doses of 2-4 mg/kg i.v. only caused mild side-effects in a minority of volunteers or patients (30%). These side-effects include: nausea, vomiting, weakness, fatigue, tremor, elevations of blood pressure and respiratory rate. Interestingly, in a placebo-controlled, randomized crossover experimental pain study, naloxone 6 mg/kg i.m. was administered to 6 healthy patients. The subjects were not able to discriminate between the subjective effects of naloxone and placebo (!)[23].

In a recent study (H-2-2012-174) we administered naloxone 2.0 mg/kg to 15 healthy subjects. Six study subjects reported mild side effects: 3 subjects experienced mild to moderate tiredness, 2 subjects experienced a frontal headache and 1 subject experienced epigastric pain. In addition, 1 subject reported intense photophobia, which lasted until the following day. During infusion of the drug, participants will be monitored with ECG and measurements of pulse oximetry, blood pressure and respiratory rate. When naloxone is given, a physician and a nurse will be present and attend the patient or volunteer if potential side effects should require any kind of treatment.

By administration of naloxone to TME-participants that have recently undergone surgery, there is a

---

B WMA Declaration of Helsinki - Ethical Principles for Medical Research Involving Human Subjects (<http://www.wma.net/en/30publications/10policies/b3/> Accessed 12/07/2014)

possibility that participants will experience short lasting pain or unpleasantness from the surgical area. This may be uncomfortable for the participant, but is essential to answer the questions asked in this study. If requested by the participant, the rapid-onset, analgesic, rescue-opioid, alfentanil, will be administered, which in less than one min completely will antagonize the effects of naloxone. Alfentanil is a well-known drug used in anesthesia for immediate relief of acute pain. Alfentanil is initially given 7-15 mikrog/kg (1-2 ml/70 kg) and is administered in a titrated fashion until the desired analgesic effect is achieved. Common dose-dependent side effects are nausea, vomiting and sedation (> 10%). During the naloxone-infusion the participant's resting pain is monitored. The naloxone-infusion is immediately stopped if the participant experiences resting pain levels  $\geq 5$  (NRS 0-10).

#### *4.2.1.2 Protracted effects*

In regard to the risk of development of a sustained pain state after the naloxone administration in individuals after impacted mandibular third molar extraction, we consider it highly unlikely (cf. page 5).

#### *4.2.1.3 Conclusion*

As the pain will dissolve rapidly spontaneously, or if necessary, after antagonizing and abolishing the effects of the study drug with alfentanil, the participant will be well-informed about the possibility that this can occur. Thus we believe there will not be significant ethical issues in this study.

The study is considered by the research group to be important, since the result will enhance our understanding of the transition from acute to persistent pain states, and thereby, may improve stratification and management strategies.

### **4.2.2 Burn injury (BI-participants)**

#### *4.2.2.1 Adverse effects*

The first degree burn injury is a moderately painful procedure inducing signs of a slight sunburn with erythema, hyperemia, hyperalgesia and hypersensitivity. These signs subside in most cases 24 to 48 hrs, without leaving residual signs. However in 1-2% of participants hyperpigmentation is evident.

If the participant experiences severe pain during induction of the burn injury the participant is able to discontinue the heating by pushing a button terminating the stimulus or by saying so to the investigator. In case of a malfunctioning, overheating contact thermode a more severe second to third degree burn injury has been described. Due to the rigorous, compulsory testing paradigms of our thermodes, we have not experienced any thermal adverse effects during the last five years with the BI-model (H-2-2010-115; H-2-2012-036; H-2-2012-174; H-1-2013-045; H-4-2013-013), including more than 350 burn injuries.

#### *4.2.2.2 Conclusion*

The investigators do not believe that there will be any significant ethical issues using the burn injury in this study.

### **4.3 Informed Consent**

#### **4.3.1 Impacted mandibular third molar extraction study (TME-participants)**

All included TME-participants have been submitted to unilateral, primary, uncomplicated, impacted mandibular third molar extraction surgery at Dept. Oral Surgery (att. senior clinical instructor [name] DDS), School of Dentistry, University of Copenhagen (section 29.1.14; [name]). The TME-participants will receive the written information about the study by the investigator before the operation. The investigator will give verbal information in a quiet room and inform the participant that he has the right to bring a relative for the information, and to have time to consider participation in the study. Two weeks ( $\pm 3$  days) after the surgery the investigator will make a telephone call, four weeks [ $\pm 3$  days] after the TME-surgery, and make an appointment with the subject for the examination days (Day 1; Day 2).

Day 1 the investigator will repeat the oral information and will answer any questions the TME-participants may have. The written consent will be obtained on Day 1 of the study before any assessments will be done. If the participant needs more time before signing the informed consent a new Day 1 will be scheduled. The participant will be informed that the participation in the study is voluntary and that they may withdraw from the study at any time without further explanation. This will not have any consequence for ongoing or future treatments at the involved departments or hospitals. In addition, the participant will be informed that the investigator may exclude them from the study at any time. TME-participants will receive an hourly payment for attending the study of 150 DKR (25 USD) and if required by the participant, reimbursement for transportation costs.

#### **4.3.2 Burn injury study (BI-participants)**

The BI-participants will be recruited from our registry of volunteers who previously have participated in experimental pain studies at the Multidisciplinary Pain Center 7612, Rigshospitalet, and, specifically, have given their verbal or written consent, that they may be contacted in future research. In addition, if the investigators experience difficulty in recruitment of participants, an advertisement will be placed in a Danish E-site for recruitment of volunteers in medical research ([forsoegsperson.dk](http://forsoegsperson.dk)).

The BI-participants will receive the written information about the study by the investigator. The investigator will schedule a physical meeting with the BI-participant and inform the participant that he has the right to bring a relative or a friend for the information meeting. At the meeting, that takes place in a quiet room, in an undisturbed environment, the investigator will then render verbal information concerning the study and answer the BI-participant's and the relative's questions. The BI-participant is informed that he has time to consider participation in the study. Two days after the meeting the investigator will call or send an E-mail, making an appointment with the BI-participant for the study day.

At the study day the investigator will repeat the verbal information and will answer any questions the BI-participants may have. The written consent will be obtained on the study day before any assessments will be done. If the BI-participant needs more time before signing the informed consent a new study day will be scheduled. The participant will be informed that the participation in the study is voluntary and

that he may withdraw from the study at any time without further notice or explanation. This will not have any consequence for ongoing or future treatments at the involved departments or hospitals. In addition, the participant will be informed that the investigator may exclude them from the study at any time. BI-participants will receive an hourly payment for attending the study of 150 DKR (25 USD) and if required by the BI-participant, reimbursement for transportation costs.

#### **4.4 Data Registration and Protection**

The trial will be reported to the Data Protection Agency. The “Act on Processing of Personal Data” will be respected. All the participants personal data will be kept confidential. All information and the reporting of individual test-results will be treated confidentially. The participant’s data will be anonymous and the persons involved in the study will adhere to the secrecy legislation.

Data collected in the form of Case Report Form, signed informed consent forms and records created for the study will only be made available for monitoring and inspection by authorized representatives of relevant authorities, including the Good Clinical Practice (GCP) unit of the Copenhagen University Hospital, the Regional Committee of Research Ethics, the Danish Health and Medicines Authority and the Danish Data Protection Agency. The study will follow the guide-lines and rules of GCP and Good Medical Practice (GMP).

## **5. TIMELINE AND LOCATION OF THE STUDY**

### **5.1 Estimated time plan (all participants)**

|                   |                                     |                   |
|-------------------|-------------------------------------|-------------------|
| Study start:      | February 1st 2016 | 01.02.2016 |
| Study completion: | March 31st 2017   | 31.03.2017 |

### **5.2 Duration of examination days**

#### **5.2.1 TME-participants**

The two examination days are identical in set-up and will require total 6 hrs of participation.

#### **5.2.2 BI-participants**

The five examination (Days 0-4) days require a total 17½ hrs of participation. Day 0 is a screening day (1½ hrs) selecting high- and low-sensitizers eligible for examination at Days 1-4. Day 1 and Day 3 are BI-days (5 hrs), and, Day 2 and Day 4 are TCI-days (11 hrs).

### **5.3 Location (all participants)**

Departments of Neuroanaesthesia 3042 and Multidisciplinary Pain Center 7612, both at Neuroscience Center, Rigshospitalet. The study takes place in a quiet room (22-25 °C, relative humidity [RH] 20-75%).

## **6. STUDY DESIGN**

### **6.1 TME-participants**

|                |                                                                                                  |
|----------------|--------------------------------------------------------------------------------------------------|
| Study type:    | Randomized, placebo-controlled, double-blind crossover                                           |
| Randomization: | Computer generated randomization list, closed envelopes                                          |
| Phase:         | Phase 2                                                                                          |
| Blinding:      | Double-blind, crossover                                                                          |
| Subjects:      | Participants with unilateral, primary, uncomplicated, impacted mandibular third molar extraction |
| Number:        | 14 evaluable subjects (maximum included number: 18)                                              |

## 6.2 BI-participants

|                |                                                         |
|----------------|---------------------------------------------------------|
| Study type:    | Randomized, placebo-controlled, double-blind crossover  |
| Randomization: | Computer generated randomization list, closed envelopes |
| Phase:         | Phase 2                                                 |
| Blinding:      | Double-blind, crossover                                 |
| Subjects:      | Healthy volunteers                                      |
| Number:        | Day 0: 80 subjects; Day 1-4: 40 evaluable subjects      |

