#### 7.1.2 BI-participants

BI-participants must meet all the following criteria to be eligible to enroll in the study Day 0:

- Healthy male
- Age above 18 yrs and below 35 yrs
- Signed informed consent
- Urin-sample *without* traces of opioids (morphine, methadon, buprenorphine, codeine, tramadol, ketobemidone, oxycodone, hydromorphone, dextromethorphan)
- ASA I

- Body mass index (BMI):  $18 < \text{BMI} < 30 \text{ kg/m}^2$

In addition, BI-participants must meet the following criteria to be eligible to further enroll in the study Day 1-4:

- Secondary hyperalgesia areasC 1 hr after a burn injury ( $47^\circ\text{C}$ ,  $2.5 \times 5.0 \text{ cm}^2$ , 7") either  $\geq 37 \text{ cm}^2$  (high-sensitizers) or  $\leq 22 \text{ cm}^2$  (low-sensitizers). The selection into high-sensitizers and low-sensitizers is made during a separate test day (Day 0).

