### 7.2.2 BI-participants

BI-participants, who meet one or more of the following criteria, are not suitable for inclusion in this study:

- Participants, who do not speak or understand Danish
- Participants, who cannot cooperate with the investigation
- Allergic reaction against morphine or other opioids (including naloxone)
- Abuse of alcohol or drugs – according to investigator's evaluation
- Use of psychotropic drugs (exception of SSRI)
- Neurologic or psychiatric disease
- Signs of neuropathy in the examination region
- Previous severe trauma to the lower legs with sequelae
- Scarring or tattoos in the examination areas
- Chronic pain condition
- Regular use of analgesic drugs
- Use of prescription drugs one week before the trial

---

C Secondary hyperalgesia areas are calculated after subtracting the primary hyperalgesia area ( $12.5 \text{ cm}^2$ ). Data from: Ringsted TK, Enghuus C, Petersen MA, [name] (2015) Demarcation of secondary hyperalgesia zones: Punctate stimulation pressure matters. J Neurosci Methods 256: 74-81.

- Use of over-the-counter (OTC) drugs 48 hours before the trial
- Does not develop measurable secondary hyperalgesia areas after BI

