#### 9.1.2 BI-study

Participants are screened during a separate day (Day 0; 1½ hrs; Fig. 3): a burn injury is induced and secondary hyperalgesia areas are assessed. The boundaries of 25% and 75% quartiles for secondary hyperalgesia areas (22 cm^2 [low-sensitizers] and 37 cm^2 [high-sensitizers], respectively [Ringsted TK, et al. (2015) J Neurosci Methods 256: 74-81]) are used to allocate participants into low-sensitizers (areas ≤ 22 cm^2) and high-sensitizers (areas ≥ 37 cm^2). Data from the 80 participants are used to determine contemporary and probably more accurate boundaries of 25% and 75% quartiles for secondary hyperalgesia areas! Only low-sensitizers and high-sensitizers continue in the study, the remaining participants are excluded.

Day 1 and Day 3 are identical testing days with induction of BI's and sensory assessments (Figs. 3-4). Day 2 and Day 4 are identical TCI-testing days (Figs. 3-4), with participants randomized and allocated to receive either placebo or naloxone.

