### 13.1.2 BI-participants

Data from our previous high-dose naloxone study (Pereira MP et al [2015] PLOS One 10: e0134441. 10.1371/journal.pone.0134441 [doi]) indicate:

1. for the high-sensitizers ( $n = 3$ ): secondary hyperalgesia areas 168 hrs after the BI during placebo infusion, mean (SD),  $2.1 \text{ cm}^2$  ( $2.5 \text{ cm}^2$ ) and during naloxone infusion  $111.0 \text{ cm}^2$  ( $26.3 \text{ cm}^2$ ).
2. for the low-sensitizers ( $n = 3$ ): secondary hyperalgesia areas 168 hrs after the BI during placebo infusion,  $0.3 \text{ cm}^2$  ( $0.1 \text{ cm}^2$ ) and during naloxone infusion  $0.9 \text{ cm}^2$  ( $0.6 \text{ cm}^2$ ).

Using the significance level  $\alpha$  set to 0.01 and the power set to  $= 0.90$  ( $\beta = 0.10$ ), the estimated number of individuals needed to reject the null hypothesis in the high-sensitizers are 5 (effect size 4.1; sic!) and in the low-sensitizers are 18 (effect size 1.4). Since the data used for sample size estimates are made on an extremely limited number of individuals, and, since the study of nature is a proof-of-concept, it was decided to include 20 high-sensitizers and 20 low-sensitizers. Boot-strapping techniques could have been used, but we considered the number individuals used in the sample estimate too extreme. On the other hand, if a larger number of subjects are needed, the clinical significance is deemed of dubious value.

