### 15.2 Financial issues

The study is partially funded by National Institute of Health (NIH-NIDA) NIH R01DA037621. Additional grants will be sought from private funds. A preliminary budget is indicated below:

|                                                   | USD              | DKR            |
|---------------------------------------------------|------------------|----------------|
| Year                                              | 1                | 1              |
| Research Associate Months                         | 5                |                |
| Research Associate's Salary                       | \$ 28,762        | 198,168        |
| Research Assistant Months                         | 5                |                |
| Research Assistant's Salary                       | \$ 7,553         | 52,037         |
| Volunteers' salaries                              | \$ 16,546        | 114,000        |
| Patients' Reimbursement TME                       | \$ 2,351         | 16,200         |
| Maintenance QST Equipment                         | \$ 2,599         | 17,907         |
| Drug costs                                        | \$ 9,289         | 64,000         |
| Miscellaneous Lab. Costs                          | \$ 1,109         | 7,638          |
| Compliance cost to Rigshospitalet Copenhagen (8%) | \$ 4,948         | 34,092         |
| Total                                      | \$ 73,156 | 504,041 |

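### In the burn injury study, 80 screened gives 40 only as the expected number eligible; the stated 40 evaluable (20 high, 20 low) leaves no margin for chance or loss

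*Protocol*

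**What the plan says.** Section 6.2 of the protocol sets the BI numbers: "Day 0: 80 subjects; Day 1-4: 40 evaluable subjects". Section 13.1.2 calculates a need of 5 high-sensitizers and 18 low-sensitizers. Because the pilot data were so few, "it was decided to include 20 high-sensitizers and 20 low-sensitizers".

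Section 7.1.2 fixes eligibility for Days 1-4 by the secondary hyperalgesia area one hour after the Day 0 burn: 37 cm² or more (high) or 22 cm² or less (low). Section 9.1.2 takes these values from an earlier study as "The boundaries of 25% and 75% quartiles for secondary hyperalgesia areas" and allocates participants by them. It adds: "Only low-sensitizers and high-sensitizers continue in the study, the remaining participants are excluded". The same section says: "Data from the 80 participants are used to determine contemporary and probably more accurate boundaries". It does not say what the new boundaries are for.

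Section 7.2.2 also excludes a volunteer who "Does not develop measurable secondary hyperalgesia areas after BI".

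No loss allowance or replacement rule is given for the BI study. The third molar (TME) study has one: 14 evaluable, 18 included (sections 6.1 and 13.1).

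**The concern.** The step from 80 to 40 is exact only if three things happen together: each tail holds exactly a quarter of those screened, nobody eligible declines, and nobody is lost. After Day 0 a participant has four more visits, with two more burns and two infusions, and Day 3 falls at least eight weeks after Day 0 (Figure 3 legend). A figure called evaluable should already allow for this.

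At stake is the size and balance of the two groups whose contrast is the BI primary comparison. A shortfall with no agreed response would also leave open what the investigators do next, including which cut-offs they use.

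**Working it through.** **The plan's own figure.** 80 × 0.25 = 20 low and 80 × 0.25 = 20 high, together 40. The stated 40 reproduces exactly, as an expected count of eligible volunteers with zero loss.

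**The budget carries the same numbers.** Hours are 1.5 for Day 0 and 5 + 11 = 16 for Days 1-4 (section 5.2.2), paid at 150 DKR per hour (section 4.3.2).

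- BI: 150 × (80 × 1.5 + 40 × 16) = 18,000 + 96,000 = 114,000 DKR. This is the line "Volunteers' salaries" in section 15.2.
- TME: 150 × 18 × 6 = 16,200 DKR, also the printed line, so the TME costing includes its drop-out allowance.

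**Chance of reaching the stated size.** Let n = 80, and let each person screened end as an evaluable high- or low-sensitizer with probability p = 0.25 × (1 − loss) for each group. The counts H and L are then trinomial:

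P(H ≥ a and L ≥ b) = Σ over h ≥ a of Bin(h; 80, p) × P[Bin(80 − h, p/(1 − p)) ≥ b].

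The total H + L is binomial (80, 2p). The protocol gives no BI loss rate, so 0%, 5% and 10% are assumptions.

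| Assumed loss | Expected per group | P(both ≥ 20) | P(total ≥ 40) | P(high ≥ 5 and low ≥ 18) |
|---|---|---|---|---|
| 0% | 20 | 24% | 54% | 74% |
| 5% | 19 | 14% | 37% | 65% |
| 10% | 18 | 7% | 22% | 54% |

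The last column uses the need calculated in section 13.1.2. It is driven almost wholly by the low group, since 5 high-sensitizers are nearly certain.

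**Sensitivity to the tail share.** The 25% comes from an earlier sample and may not hold here.

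| True share per tail | P(both ≥ 20), no loss | P(both ≥ 20), 10% loss |
|---|---|---|
| 23% | 10% | 2% |
| 25% | 24% | 7% |
| 28% | 55% | 26% |
| 30% | 73% | 44% |

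The exclusion of volunteers with no measurable area can only shrink the low tail, but the protocol gives no rate for it.

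**Effect on the high-versus-low contrast.** For a two-sample comparison at two-sided alpha 0.01 and power 0.90, the detectable standardized difference is 1.28 with 20 and 20, 1.35 with 18 and 18, and 1.36 with 16 and 20. That is a rise of 6-7% (1.35/1.28 ≈ 1.06; 1.36/1.28 ≈ 1.07).

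**Screening needed for an 80% chance of 20 and 20 evaluable,** at 25% per tail: 100 with no loss, 106 with 5% loss, 112 with 10% loss.

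**The case against.** The sum is right: half of 80 is 40. Nor does the protocol call 80 a ceiling. Where it means one it says so, as with the TME maximum of 18. Section 4.3.2 allows advertising if recruitment is difficult, and nothing forbids screening an eighty-first volunteer. All of this stands. Section 9.1.2 does refer to the 80 as a settled number, but a reader should not infer a hard cap from that.

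A reader might also take the exact budget match as proof that no reserve exists. Section 15.2 calls the budget preliminary and says further grants will be sought. It shows what was costed; it is not a recruitment rule.

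The strongest objection is about consequence. The calculated need is 5 and 18, not 20 and 20, and losing two per group changes the detectable difference little. That also stands, and it keeps the point moderate. It does not remove it: 13.1.2 chose 20 because the pilot had three per group, not as an allowance for loss, and even 18 low-sensitizers are far from assured.

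Finally, one might infer that the quartiles of the 80 will be used to regroup participants after treatment. The text does not say so. Sections 7.1.2 and 9.1.2 both allocate by 22 and 37 cm², and 9.1.2.1 allocates on Day 0, before all 80 could have been measured. The gap is only that the purpose of the new boundaries is unstated.

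**Conclusion.** The point holds as a mismatch between two stated numbers: the screening number delivers the evaluable number only on average and only with no loss. At 25% per tail, the 20-and-20 split is missed about three times in four with no loss (100% − 24% = 76%) and in 86% to 93% of cases at 5% to 10% loss. The total of 40 alone is close to an even chance with no loss.

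These figures rest on assumed loss rates and on the earlier study's quartiles applying here. With 28% to 30% per tail and no loss, the chance of 20 and 20 would be 55% to 73%. The protocol gives no reason to expect larger tails. The practical damage is moderate and falls mainly on the low-sensitizers, where the margin over the calculated need is two people. The stated size should be corrected or the rule behind it stated; the design itself is not undermined.

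**What to change.** Choose one of the following in section 6.2 and carry it into 13.1.2.

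1. **Keep 80 and restate the yield.** For example: 80 screened, about 40 expected eligible, about 36 expected evaluable (18 per group, assuming 10% loss). 80 × 0.25 × 0.90 = 18. Label these as expected values. This costs wording only.
2. **Keep 20 and 20 evaluable and make 80 an estimate.** State that screening continues until each group has 20 evaluable, closing a group when it is full, up to a stated cap. At 25% per tail, 100 to 112 screened gives about an 80% chance at 0% to 10% loss. The payment is 1.5 × 150 = 225 DKR per extra volunteer, plus staff time. The real cost is that 20 to 32 more healthy volunteers receive a Day 0 burn, so the first option is the cheaper one.

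Under either option, add one sentence to 9.1.2: 22 and 37 cm² define the groups for eligibility and for every analysis, and quartiles from the screened sample are descriptive only.
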